### Phase 2: evaluation of HEAL-D; a culturally tailored T2D self-management programme for African and Caribbean communities

In phase 2, a feasibility study, with an embedded process evaluation, will be conducted to address the following objectives:Evaluate the HEAL-D intervention, particularly its theoretical under-pinning, acceptability, fidelity, issues of implementation and sustainability.Evaluate the feasibility of trial procedures, considering issues such as rates of recruitment, retention, completion and contamination.Estimate the effect size of potential trial outcomes including HbA1c, weight, waist circumference, blood pressure, dietary intake, physical activity levels, diabetes knowledge and quality of life, to inform an effectiveness trial.

### Study design

The feasibility study will use a randomised controlled design, with individual patients as the unit of randomisation, evaluating HEAL-D against usual care. In addition, there will be a cohort of phase 1 codesign patients who will be allocated to the intervention arm (not randomised) because their involvement in the intervention design phase would contaminate the control arm. These patients will be included in the feasibility study to enable us to evaluate the impact of former involvement on intervention engagement, acceptability and ownership.

### Participants

Participants will principally be recruited from general practice in the London Boroughs of Lambeth and Southwark through screening of referrals for structured education and letters of invitation to patients with established T2D. In addition, participants from the phase 1 codesign study will be invited to participate, and self-referral methods will also be used, for example, posters and advertisements in community locations.

Patients with diagnosed T2D who are of African or Caribbean ethnicity and with capacity to provide fully informed consent to participation in research will be eligible to participate in the trial. Ethnicity will be self-declared using the standard NHS ethnicity categorisation questionnaire. Patients who are unable to communicate in English and patients with complex therapeutic dietary needs may be ineligible to participate if their individual needs are deemed incompatible with the aims of the intervention. This is because the intervention will provide general diet and lifestyle advice for the self-management of T2D in a group setting; in cases of patients with certain comorbidities, for example, advanced renal disease, the intervention may be inappropriate for the individual, and the group nature of the intervention will prevent their individual needs from being addressed.

A pragmatic sample size of 120 patients is anticipated to be sufficient to evaluate the programme, allowing for 20% dropout/non-completion; 80 patients will be randomised, 40 in each arm, and a further cohort of patients (n=40) from phase 1 will be allocated to the intervention arm without randomisation. As this is a feasibility trial, it will not be powered to detect statistically significant intervention effects. A primary objective of the study is to provide estimates of key parameters such as potential effect sizes, recruitment and retention rates of the trial and participation rates of the programme to enable the optimal design of a full-scale trial to be determined.

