#### Estimating the effect of the intervention on potential trial outcomes

Participants will attend a baseline and postintervention follow-up assessment visit, conducted by a research technician, at 26–32 weeks to collect the following potential trial outcomes and estimate effect sizes:

Biomedical outcomes: a 5 mL venous blood sample will be taken for analysis of HbA1c and total HDL-cholesterol and LDL-cholesterol and triglycerides. Systolic and diastolic blood pressure will be measured using an automated sphygmomanometer.

Anthropometric outcomes: body weight will be measured using digital scales, with the patient wearing light clothing (without shoes); height will be measured, using a stadiometer, without shoes; body mass index will be calculated as (weight [kg]/height [m^2^]). Waist circumference will be measured with the patient wearing only light clothing, at the midpoint between the lowest rib and the iliac crest.

Diet and physical activity behaviour outcomes: dietary intake will be assessed through completion of a 24-hour diet recall, using the structured multiple pass interview method, and physical activity through 3-day Actiwatch accelerometer assessment and completion of the International Physical Activity Questionnaire.

The following validated self-complete questionnaires will be administered to assess: diabetes knowledge (Short Diabetes Knowledge Instrument^40^); diabetes and diet knowledge and competence (Perceived Diabetes & Dietary Competence^37^); empowerment (Diabetes Empowerment Scale-Short Form^41^); social support (Multidimensional Scale of Perceived Social Support^42^); diabetes distress (problem areas in diabetes (PAID)-5^43^); and quality of life (EuroQol (EQ)-5D-3L^44^).

Statistical analysis: given that this is a feasibility study with a small sample size, descriptive statistics will be used (χ^2^ test and Fisher’s exact test). Differences between the groups in all outcomes will be estimated with 95% CIs. The descriptive data will provide stable estimates of the variability of continuous outcomes by group and provide estimates of differences between the groups in means and proportions for the key outcomes. The SD of the mean change in HbA1c will be estimated by arms and used to derive the sample size calculation for a subsequent trial.

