##### Retention and completion

We will assess the rate of retention both within the HEAL-D intervention (ie, numbers completing each session and the full programme) and the feasibility trial (ie, numbers completing baseline and endpoint assessment visits). We will evaluate the feasibility of randomising and retaining a control arm by assessing dropout rates and comparing these between the study arms; we will also interview control arm patients to explore the acceptability of being assigned to the control arm.

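### Read literally, 40 non-randomised codesign patients count in the intervention arm for the effect and dropout comparisons, which should be limited to the 80 randomised patients

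*Protocol article*

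**What the plan says.** The Study design section sets out the comparison: "The feasibility study will use a randomised controlled design, with individual patients as the unit of randomisation, evaluating HEAL-D against usual care". It then adds a group of phase 1 codesign patients who join the intervention arm without randomisation, "because their involvement in the intervention design phase would contaminate the control arm". Their stated purpose is to show how earlier involvement affects engagement with the programme, its acceptability and the sense of ownership.

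The Participants section gives the numbers. "A pragmatic sample size of 120 patients is anticipated to be sufficient to evaluate the programme", with an allowance of 20% for dropout. Of these, "80 patients will be randomised, 40 in each arm". The remaining 40 enter by another route: "a further cohort of patients (n=40) from phase 1 will be allocated to the intervention arm without randomisation". Effect sizes and retention rates are named there as key parameters that the study must supply for a full-scale trial.

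The estimation rules come later:

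- Statistical analysis paragraph: "Differences between the groups in all outcomes will be estimated with 95% CIs". The same paragraph has the SD of HbA1c change estimated for each arm and carried into the sample size of the later trial.
- Retention and completion: dropout rates are assessed by "comparing these between the study arms", to judge whether a control arm can be randomised and retained.

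No section limits these estimates to the 80 randomised patients or makes the codesign cohort an analysis group of its own.

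**The concern.** The article assigns the cohort to the intervention arm in two places and then estimates by arm or group. Someone applying those sentences as written would compare 80 intervention patients with 40 controls. Half of the intervention patients could never have been controls, and the article itself regards them as already exposed to the programme's content. Patients in a future trial would not have helped to design the programme.

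At stake is a main output of the study. It is not powered to test an effect, so its quantitative value lies in the estimates that it passes on. A pooled effect estimate would mix the randomised contrast with selection and prior exposure, and its CI would be narrower than the randomised data can support. A pooled dropout comparison would not answer the question that it is meant to answer.

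**Working it through.** **Inputs from the Participants section:** 40 randomised per arm, 40 codesign patients, 20% dropout. **Assumed, because the article gives no figure:** d, the difference in mean outcome between codesign and randomised intervention patients, in SD units, taken over 0.2 to 0.5. Dropout is taken as equal across the three groups except in step 5.

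**1. The plan's own total.** 40 + 40 + 40 = 120, and 120 × 0.8 = 96 completers (32 per block). The stated sample size reproduces. The fault lies in the analysis set, not in this sum.

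**2. Bias in the effect.** The codesign share of the arm is 40/80 = 0.5, so bias = 0.5 × d.

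**3. Precision.** SE = SD × √(1/n₁ + 1/n₂), and the 95% half-width is 1.96 × SE.

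- Pooled, 64 v 32: √(1/64 + 1/32) = 0.2165 SD; half-width 0.42 SD.
- Randomised only, 32 v 32: √(1/32 + 1/32) = 0.250 SD; half-width 0.49 SD.
- Ratio: 0.250/0.2165 = 1.155, so the randomised CI is about 15% wider.

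**4. Coverage of the pooled CI for the randomised effect.** With bias b, coverage = Φ(1.96 − b/0.2165) − Φ(−1.96 − b/0.2165).

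| d (SD) | Bias b (SD) | Coverage of nominal 95% CI |
|---|---|---|
| 0.2 | 0.10 | 0.925 |
| 0.3 | 0.15 | 0.893 |
| 0.5 | 0.25 | 0.789 |

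Allowing for the slightly larger SD of a mixed arm changes these only to 0.926, 0.895 and 0.795. Coverage is the same whether the bias is positive or negative.

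**5. Dropout (rates assumed for illustration).**

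- Randomised intervention 30%, codesign 10%, control 20%: the pooled arm loses (12 + 4)/80 = 20%. The comparison shows no difference and hides a randomised difference of 10 points.
- Randomised intervention 20%, codesign 10%, control 20%: the pooled arm loses (8 + 4)/80 = 15%. The comparison shows a 5-point advantage where the randomised arms do not differ.

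**6. SD of the mixed arm.** For an equal mixture, the SD is multiplied by √(1 + d²/4). At d = 0.2 this is √1.01 = 1.005; at d = 0.5 it is √1.0625 = 1.031. The control-arm SD is untouched.

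**The case against.** The strongest reply is that the article never says the 40 will be pooled. It calls the trial a randomised comparison, introduces the codesign patients as an addition, and gives them a purpose that can be met only by separating them from the randomised intervention patients. It states no arm total of 80, leaves the groups in the analysis paragraph undefined, and condenses a fuller protocol. An unseen analysis plan may already separate the cohort.

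Much of this stands: pooling follows from the wording but is not an announced intention. It does not dispose of the point. The article does more than leave a detail open: it fixes who belongs to the intervention arm and then estimates by arm. A later plan that separated the cohort would have to depart from those sentences.

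A reader might also infer four stronger things that the document does not support:

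- **That the bias favours HEAL-D.** Codesign patients may be more engaged, but earlier involvement may also have changed behaviour before the phase 2 baseline and so left less room for change. The recruitment contrast is partial too: phase 1 also recruited through general practices, and phase 2 also uses community advertising and self-referral.
- **That the SD is invalid.** An SD is not a randomised comparison, and mixing inflates it by only about 0.5% to 3%. The remaining objection is that it would describe a mixture unlike a future trial's patients.
- **That the definitive trial would be underpowered by a stated amount.** This needs a true effect and a rule for sizing on the observed effect. The article gives neither; the only input that it ties directly to the sample size calculation is the SD of HbA1c change.
- **That the cohort must never be pooled for any purpose.** Describing everyone who attended HEAL-D, for fidelity, attendance and acceptability, is legitimate.

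**Conclusion.** The concern holds for the effect and dropout comparisons. Followed as written, both cease to be randomised comparisons, and they feed a primary objective of the study. Half of any codesign-versus-randomised difference enters the effect estimate. The range in step 4 rests on the assumed d, on equal dropout of 20% and on a normal approximation; the true d and its sign are unknown. If d were zero, the pooled effect estimate would be unbiased, but nothing in the design ensures that. The dropout figures show only that confounding can either hide or create a difference. The SD is a minor part of the point.

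That the trial is an unpowered feasibility study does not remove the fault, because estimation is its purpose. The article does not show that the investigators intend to pool; it shows that the wording directs a literal reader to do so.

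**What to change.** - **Statistical analysis paragraph:** state that between-arm effect estimates and the HbA1c-change SD for the future sample size use only the 80 randomised patients, as allocated (40 v 40).
- **Retention and completion:** state the same for the comparison of dropout between intervention and control.
- **Both places:** report the codesign cohort separately for these outcomes, as a non-randomised group.
- **Participants:** describe the sample as 80 randomised patients plus a separate non-randomised cohort of 40.
- **Keep:** pooled description of all HEAL-D attendees for fidelity, attendance and acceptability, and the contrast of codesign with randomised intervention patients that the Study design section calls for.

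The change takes a few sentences and one table column. It needs no extra patients and no change to recruitment, randomisation or data collection. The price is the wider interval shown in step 3, which is the precision that the randomised data actually provide. If separate analysis was always intended, the text merely says so.

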### Intervention and control arms

Participants in the control arm will continue with usual care deemed appropriate and delivered by their primary care team, which may include referral to group structured education and/or one-to-one consultations with healthcare professionals.

Participants in the intervention arm will be offered the HEAL-D programme, which will deliver a curriculum of culturally tailored, evidence-based diet and physical activity education and behaviour change in a group setting. In line with clinical guidelines, the programme will be delivered by trained educators (external to the research team); favoured educators (eg, lay educators vs healthcare professionals) will be identified in the codesign process. The details of each session, particularly the behaviour change techniques and corresponding activities/materials, will be identified through the codesign work.

The proposed curriculum will map to evidence-based guidelines and will be as follows:An introduction to T2D self-management principles.Physical activity in T2D management.Carbohydrates and portion sizes.Weight management for T2D.Managing cardiovascular health.

In line with clinical guidelines for diabetes structured education, the education sessions will be delivered through educator-led interactive discussion; however, support materials will be provided to reinforce the learning, detailing evidence-based diet and physical activity guidance, which is culturally tailored for the African and Caribbean communities.

### Data collection

We will use a mixed methods approach, collecting a range of quantitative and qualitative data, to evaluate the intervention and the feasibility of trial procedures.

#### Estimating the effect of the intervention on potential trial outcomes

Participants will attend a baseline and postintervention follow-up assessment visit, conducted by a research technician, at 26–32 weeks to collect the following potential trial outcomes and estimate effect sizes:

Biomedical outcomes: a 5 mL venous blood sample will be taken for analysis of HbA1c and total HDL-cholesterol and LDL-cholesterol and triglycerides. Systolic and diastolic blood pressure will be measured using an automated sphygmomanometer.

Anthropometric outcomes: body weight will be measured using digital scales, with the patient wearing light clothing (without shoes); height will be measured, using a stadiometer, without shoes; body mass index will be calculated as (weight [kg]/height [m^2^]). Waist circumference will be measured with the patient wearing only light clothing, at the midpoint between the lowest rib and the iliac crest.

Diet and physical activity behaviour outcomes: dietary intake will be assessed through completion of a 24-hour diet recall, using the structured multiple pass interview method, and physical activity through 3-day Actiwatch accelerometer assessment and completion of the International Physical Activity Questionnaire.

The following validated self-complete questionnaires will be administered to assess: diabetes knowledge (Short Diabetes Knowledge Instrument^40^); diabetes and diet knowledge and competence (Perceived Diabetes & Dietary Competence^37^); empowerment (Diabetes Empowerment Scale-Short Form^41^); social support (Multidimensional Scale of Perceived Social Support^42^); diabetes distress (problem areas in diabetes (PAID)-5^43^); and quality of life (EuroQol (EQ)-5D-3L^44^).

Statistical analysis: given that this is a feasibility study with a small sample size, descriptive statistics will be used (χ^2^ test and Fisher’s exact test). Differences between the groups in all outcomes will be estimated with 95% CIs. The descriptive data will provide stable estimates of the variability of continuous outcomes by group and provide estimates of differences between the groups in means and proportions for the key outcomes. The SD of the mean change in HbA1c will be estimated by arms and used to derive the sample size calculation for a subsequent trial.

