	Patient questionnaires	Session observations	Session record of activities	Patient evaluation forms	Educator interviews	Patient interviews	Patient focus groups	Attendance records	HCP interviews	Commissioner interviews	
Testing intervention theory and mechanisms of change											
Are the intervention’s mechanisms of change operationalised as hypothesised?	X	X	X	X	X	X	X				Qualitative data collected through interviews/focus groups with patients and educators, and session observation notes will be used to evaluate how the theory of the intervention operationalises and interacts with contextual factors.
How is the operationalisation of the mechanisms of change influenced by contextual factors?		X	X		X	X	X				
Does the interaction of the mechanisms of change with contextual factors give rise to unintended effects?		X	X		X	X	X				
Assessing usual practice and contamination											
Is HEAL-D differentiable from ‘usual practice’?						X					Interviews will be conducted with patients from both arms. Experiences of the intervention and control will be explored. With control patients issues of contamination and perceptions of ‘usual care’ will be discussed.
Is there contamination in control patients?						X					
Assessing implementation											
What is the intervention reach and dose?	X							X			Questionnaire data will assess who receives the intervention and how representative they are, for example, age, gender, ethnicity and working status. Attendance records will be used to quantify the proportion of patients receiving the full versus part intervention.
Are the HEAL-D components/sessions delivered with fidelity and what is the nature of any adaptions?		X	X		X						To assess fidelity and compare intervention deliveries and contextual impacts educators will complete a record of activities and materials and list any resources/activities/discussions that were additional to the standardised schedule. These will be explored in depth in educator interviews that will be conducted at the end of the programme delivery. The research team will observe HEAL-D delivery to quantitatively assess coverage of curriculum, use of supporting materials and behaviour change techniques, quality of delivery and participant engagement (binary score or a 5-point Likert scale). Observers will qualitatively document course adaptations and general contextual observations.
Does the delivery of HEAL-D differ between sites, and what gives rise to differences?		X	X		X						

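### HEAL-D is taught in groups to individually randomised patients, but neither the analysis nor the stated sample-size input for the next trial allows for correlation within those groups

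*Protocol article*

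**What the plan says.** All references are to the protocol article.

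- **Study design:** the trial is randomised "with individual patients as the unit of randomisation, evaluating HEAL-D against usual care".
- **Intervention and control arms:** HEAL-D is "culturally tailored, evidence-based diet and physical activity education and behaviour change in a group setting", and "the programme will be delivered by trained educators (external to the research team"). The size and number of groups and the number of educators are not given. Control patients receive usual care, "which may include referral to group structured education and/or one-to-one consultations with healthcare professionals".
- **Evaluation of the HEAL-D intervention, Table 1:** one process question is "Does the delivery of HEAL-D differ between sites, and what gives rise to differences". It is to be answered from observations, session records and educator interviews.
- **Estimating the effect of the intervention on potential trial outcomes, statistical analysis paragraph:** after naming χ² and Fisher's exact tests, it says "Differences between the groups in all outcomes will be estimated with 95% CIs". It then says "The SD of the mean change in HbA1c will be estimated by arms and used to derive the sample size calculation for a subsequent trial".
- **Participants:** 80 patients are randomised, 40 to each arm, and 40 phase 1 patients join the intervention arm without randomisation. The allowance for dropout is 20%. The study is not powered for effects, but providing estimates from which a full-scale trial can be designed is a primary objective.

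**The concern.** Patients are randomised one by one, but those allocated to HEAL-D are then taught together by shared educators. This is an individually randomised group-treatment design. Patients in the same HEAL-D group may have more similar outcomes than patients in different groups, because they share an educator, a venue and each other. The article itself asks whether delivery varies between sites, so variation between deliveries is a live question.

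With a positive correlation, the mean of the intervention arm is less precise than its number of patients suggests. Two results follow. Confidence intervals that ignore grouping are too short. More importantly for a feasibility study, a definitive trial sized from the SD alone lacks a term it needs. Sizing that trial is a declared purpose of this study, and the sentence that names the input names only the SD.

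**Working it through.** **1. The plan's own figure.** 40 + 40 + 40 = 120, as stated. With 20% loss, 120 × 0.8 = 96 complete, of whom 40 × 0.8 = 32 are in each randomised arm. No effect size, SD or power is given, so there is no power calculation to reproduce.

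**2. Assumptions not in the article.** Group size m = 8 or 10; ICC = 0.01 or 0.05; equal outcome variance in the two arms; clustering in the intervention arm only; 1:1 allocation. For the power figures, 90% planned power at two-sided 5%.

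**3. Formulas.**
- Design effect in the intervention arm: DE = 1 + (m − 1) × ICC.
- Variance of the difference between arms relative to independence: v = (DE + 1)/2. The required total N is multiplied by the same v.
- Half-width of the 95% CI with 32 per arm: 1.96 × √(2/32) = 0.490 SD under independence, multiplied by √v with clustering.
- True coverage of an interval that ignores clustering: 2Φ(1.96/√v) − 1.
- Power of a trial sized for 90% without the design effect: Φ(3.24/√v − 1.96), where 3.24 = 1.96 + 1.28.

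**4. Results.**

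| m | ICC | DE | v | Rise in N | Half-width (SD) | Coverage | Power if 90% planned |
|---|---|---|---|---|---|---|---|
| 8 | 0.01 | 1.07 | 1.035 | 3.5% | 0.499 | 94.6% | 89% |
| 10 | 0.01 | 1.09 | 1.045 | 4.5% | 0.501 | 94.5% | 89% |
| 8 | 0.05 | 1.35 | 1.175 | 17.5% | 0.531 | 92.9% | 85% |
| 10 | 0.05 | 1.45 | 1.225 | 22.5% | 0.542 | 92.3% | 83% |

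For the last row: DE = 1 + 9 × 0.05 = 1.45; v = 2.45/2 = 1.225; √v = 1.107; power = Φ(3.24/1.107 − 1.96) = Φ(0.97) = 0.83.

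In patients, for an assumed standardised effect of 0.3 and 90% power: 234 per arm under independence, 242 to 245 at ICC 0.01, and 275 to 287 at ICC 0.05.

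**5. Is the SD itself wrong?** Hardly. In simulation with four groups of 8 and a true ICC of 0.05, the estimated variance averaged 1.2% low. What is missing is the design effect.

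**6. Could this study supply the ICC?** No. Four groups of 8 make up the 32 randomised completers in the intervention arm. In that simulation the estimated ICC ran from about −0.13 to 0.34 (2.5th to 97.5th percentile) when the truth was 0.05.

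**The case against.** - **The interval method is not stated.** A reader might infer that the intervals treat patients as independent. The χ² and Fisher tests do assume this, but they do not fix the intervals for continuous outcomes, and an analysis plan that is not shown could adjust them. This stands: the point about intervals can only be conditional.
- **Naming the SD does not exclude a design effect later.** This is true, and no sample size or power is stated for the next trial; the 90% above is an assumption. So the documents do not show that the next trial will be undersized. But the sentence names its input, and that input is incomplete for a group-delivered programme.
- **Controls may also be taught in groups.** A reader might take clustering to be confined to the intervention arm. Usual care can include group structured education, so clustering is mainly, not necessarily only, in the HEAL-D arm. The one-arm formula is an approximation.
- **The mechanism is not settled.** It is tempting to say the plan expects peer influence. The section on theoretical basis says only that social learning theory may be relevant, with codesign still to come.
- **The effect may be small.** At an ICC of 0.01 it is. The phase 1 patients could dilute it further in this study's randomised comparison: if they made up half of each group (an assumption), groups of 8 to 10 would hold 4 to 5 randomised patients, and at an ICC of 0.05 v falls to 1.075 to 1.10.
- **A mixed model on a handful of groups adds little to a descriptive analysis.** Largely accepted. That is why the weight falls on the sample-size sentence, and why a sensitivity analysis is enough here.

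**Conclusion.** The point holds in conditional form. Individual randomisation, group delivery and a sample-size input that names only the SD are all in the text. The direction follows for any positive ICC; at zero nothing changes. The size rests on an assumed ICC and group size: negligible at 0.01, but enough at 0.05 to matter for a definitive trial. For the present unpowered study the effect on the intervals is modest, from about 2% to 11% wider across the four cases. The sample-size input is the stronger half, because it bears on a primary objective. This is a change that should be made, not a flaw that undermines the feasibility study.

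**What to change.** 1. Record the HEAL-D group, educator and site for every intervention patient, and any group education that control patients attend. Attendance records are already planned; membership is hard to reconstruct later.
2. Report differences between arms with intervals that allow for HEAL-D group membership, using a small-sample degrees-of-freedom correction, at least as a sensitivity analysis.
3. Amend the sample-size sentence so that the next trial uses the SD of change together with a design effect of 1 + (m − 1) × ICC on the intervention arm. Take m from the group sizes observed, and vary the ICC over an assumed range such as 0.01 to 0.05. Do not use the ICC fitted here as a single planning value.

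The cost is a few data fields, one extra analysis and one amended sentence. The downside is slightly wider intervals and a somewhat larger projected definitive trial.

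### HbA1c effect estimate and planning SD do not use the measured baseline: a baseline-adjusted difference and residual SD among the randomised patients would serve the next trial better, at no cost in data

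*Protocol article*

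**What the plan says.** All analysis statements are in the Protocol article, section *Estimating the effect of the intervention on potential trial outcomes*.

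- Measurement: "Participants will attend a baseline and postintervention follow-up assessment visit". HbA1c, lipids, blood pressure, weight, waist, diet, activity and the questionnaire scores are collected at these visits.
- Type of analysis: "given that this is a feasibility study with a small sample size, descriptive statistics will be used".
- Effect estimates: "Differences between the groups in all outcomes will be estimated with 95% CIs". The data are to "provide estimates of differences between the groups in means and proportions for the key outcomes".
- Planning input: "The SD of the mean change in HbA1c will be estimated by arms and used to derive the sample size calculation for a subsequent trial".

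The section *Participants* gives the numbers: "A pragmatic sample size of 120 patients is anticipated to be sufficient to evaluate the programme", of whom "80 patients will be randomised, 40 in each arm", with a 20% allowance for dropout or non-completion. A further phase 1 cohort joins the intervention arm without randomisation. The same section makes it a primary objective to estimate the parameters needed to choose the best design for a full-scale trial.

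The Abstract names HbA1c and body weight as potential primary outcomes. A planning SD is named for HbA1c only. The article mentions no baseline-adjusted model, baseline-to-follow-up correlation or residual SD.

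**The concern.** The main quantitative products of this study are an effect estimate and a variance for the next trial. Both are described in a form that does not use the baseline measurement as a covariate.

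For the effect estimate, about 32 analysed patients per arm leave room for a visible chance difference in baseline HbA1c. Recruitment mixes referrals for structured education with patients who have established diabetes, and the article states no HbA1c limits, so baseline values may be widely spread. A difference in follow-up means keeps part of any baseline imbalance. A difference in change scores over-corrects for it, through regression to the mean.

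For the variance, a definitive trial analysed with baseline adjustment needs the residual SD, which is smaller than the SD of change. If only the latter is carried forward, that trial would recruit more patients than it needs.

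**Working it through.** **1. The plan's own figures.** 40 + 40 + 40 = 120. With 20% loss, 120 × 0.8 = 96 overall. Assuming the loss is even, 40 × 0.8 = 32 remain per randomised arm and 64 in the randomised comparison. The total is called pragmatic and has no SD, target difference, alpha or power behind it, so there is no sample-size formula to reproduce.

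**2. Variances.** Let s be a common SD at baseline and follow-up, and rho the correlation between them. Both are assumptions, as the article gives neither.

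- Variance of individual change: 2(1 − rho)s²
- ANCOVA residual variance: (1 − rho²)s²
- Ratio, which is also the ratio of sample sizes: 2(1 − rho)/(1 − rho²) = 2/(1 + rho)

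The direction does not need equal SDs. With baseline SD s0 and follow-up SD s1, change variance minus residual variance is s0² + s1² − 2·rho·s0·s1 − (1 − rho²)s1² = (s0 − rho·s1)², which is never negative.

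**3. Excess from sizing on the SD of change when the analysis is ANCOVA.** The illustration assumes a difference of 0.4s, two-sided 5% and 90% power: n per arm = 2 × 10.507 × variance / 0.16s².

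| assumed rho | residual SD / change SD | excess, 2/(1+rho) − 1 | n per arm, change SD | n per arm, residual SD |
|---|---|---|---|---|
| 0.5 | 0.87 | 33% | 132 | 99 |
| 0.7 | 0.92 | 18% | 79 | 67 |
| 0.8 | 0.95 | 11% | 53 | 48 |

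Outside this range the excess is 54% at rho 0.3 and 5% at rho 0.9.

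**4. Dependence on chance imbalance.** With 32 per arm the baseline difference has SD s√(2/32) = 0.25s. Given a baseline difference D, the expected shift is rho·D for follow-up means, −(1 − rho)·D for change scores, and zero for ANCOVA. A simulation with 32 per arm and no true effect (20,000 runs, s = 1) agrees:

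| assumed rho | correlation with imbalance: follow-up / change / ANCOVA | SD of estimate: follow-up / change / ANCOVA |
|---|---|---|
| 0.5 | +0.50 / −0.50 / 0.00 | 0.248 / 0.248 / 0.217 |
| 0.7 | +0.70 / −0.39 / 0.00 | 0.250 / 0.195 / 0.181 |
| 0.8 | +0.80 / −0.31 / 0.00 | 0.250 / 0.157 / 0.151 |

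The ANCOVA figures include the cost of estimating the slope from 64 patients.

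**5. Sampling error of the SD, for scale.** From the chi-square interval, an SD pooled over 64 completers (62 df) has a 95% interval of 0.85 to 1.21 times the estimate. On sample size that is 0.72 to 1.47 times. For one arm alone (31 df) the factors are 0.80 to 1.33 on the SD and 0.64 to 1.77 on sample size.

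**The case against.** The case for leaving the plan alone has real force.

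- *Adjustment is not excluded.* The article never calls the differences unadjusted, and covariates are often left to an analysis plan, which is not shown here. This stands. A reader might infer that the plan rules out adjustment, but the text only describes descriptive differences in means. The planning SD is different: it is a stated choice and does not depend on this inference.
- *Change scores are not the effect estimator.* A reader might also infer that effects will be estimated from change scores. Change appears only in the sentence on the HbA1c planning SD. The working therefore covers both possible readings of a difference in means and does not attribute either to the plan.
- *The SD of change is not the wrong variance.* It is the right input for a trial analysed on change, and the article does not describe the next trial's analysis. Oversizing arises only if that trial adjusts for baseline, and it then costs extra patients, not power. This stands.
- *The correlation may be recoverable.* The section promises estimates of the variability of continuous outcomes by group. If that covers both visits, rho = (s0² + s1² − sc²)/(2·s0·s1), where sc is the SD of change, and the residual SD follows. This is a fair point, but the article does not say that both visits are covered, and reporting rho directly is simpler.
- *This is a feasibility study.* Under randomisation an unadjusted difference is unbiased and its CI already allows for chance imbalance. That is true, so adjustment is a gain in efficiency and not the repair of a bias.
- *Sampling error is at least as large.* This is also true, but that error is random, whereas the excess runs in one direction and can be avoided without new data.

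On the wording, a reader might take the SD of a mean literally as a standard error and infer a grossly undersized next trial. The sentence says that the quantity will feed a sample-size calculation, so the SD of individual changes is plainly meant.

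**Conclusion.** The point holds as an improvement to a stated method. Among the randomised patients, a baseline-adjusted difference is free of dependence on chance imbalance in the measured baseline. Its residual variance is never larger than that of follow-up means or change scores, apart from the small cost of estimating one slope.

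If the definitive trial adjusts for baseline, planning on the SD of change inflates it by about 11% to 33% for rho of 0.8 to 0.5. That range rests on an assumed rho and on equal SDs at the two visits. It is conservative, and comparable to or smaller than the uncertainty in the SD itself (0.72 to 1.47 times on sample size with both arms pooled).

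Adjustment does nothing for selection in the non-randomised cohort ("n=40) from phase 1 will be allocated to the intervention arm without randomisation"), so the benefit is limited to the 80 randomised patients.

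**What to change.** 1. For continuous outcomes, and at least for HbA1c and body weight, report the difference between the randomised arms from an ANCOVA (follow-up value on arm, adjusted for its baseline value) with a 95% CI. The descriptive means can stay alongside it.
2. For the same outcomes, report the SD of individual values, the baseline-to-follow-up correlation and the ANCOVA residual SD, each with a CI.
3. State that the SD used to size the next trial will match that trial's intended analysis: the residual SD if it adjusts for baseline, the SD of change if it analyses change.
4. Minor wording: refer to the SD of individual change in HbA1c, not of the mean change.

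The cost is a few sentences of analysis text and one extra model parameter per outcome. No visit, measurement or patient is added.
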